## Abstract

**Background:**

Suicide-related behaviour among young people is of significant concern, yet little is known regarding the effectiveness of interventions designed to reduce risk among this population. Of those interventions that have been tested, cognitive-behavioural therapy appears to show some promise among young people with suicidal ideation. Internet-based interventions are becoming increasingly popular and have shown some effect in preventing and treating depression and anxiety in young people. However, to date there are no randomised controlled trials examining the impact of Internet-based Cognitive Behavioural Therapy among suicidal youth.

**Methods/design:**

This is a randomised controlled trial testing the effects of Internet-based cognitive-behavioural therapy among suicidal high school students who have sought help from the school wellbeing team. The intervention comprises 8 modules of Cognitive Behavioural Therapy delivered online. The study has a staggered, two-year recruitment phase and participants are assessed at baseline, post intervention and 12 weeks later.

**Discussion:**

If effective the program has the ability to be readily adapted and delivered to a range of populations in a range of settings, at relatively little cost. It can also be adapted for mobile applications.

**Trial registration:**

ACTRN12613000864729. Date registered: 05/08/2013

## Background

Suicide-related behaviours (SRB), including suicide attempts (SA) and suicidal ideation are common among young people. Up to 24% of 12–17 year-olds have reported suicidal ideation, and 7-11% have reported a 12-month prevalence of suicide attempt [1]. These behaviours are one of the greatest concerns for Australian young people [2] and are associated with a range of negative outcomes including completed suicide and premature mortality via other causes [3,4]. The prevention of suicide, and the development of a strategic research agenda targeting interventions for suicidal youth have both been cited as national priorities [5,6], yet there remains a lack of high quality intervention research for suicidal individuals [7], including youth [8].

Depression is the most common risk factor for SRB. Suicidal youth are six times more likely to have a psychiatric disorder than non-suicidal youth [9-11]. The most common disorder is depression, with between 60 and 80% of young people having a diagnosis of depression at the time of a SA [12]. Hopelessness has long been linked to increased suicide risk, including among young people, and is believed to mediate the relationship between depression and suicide-related behaviour [13,14].

Notwithstanding this, not all suicidal young people experience symptoms of depression; therefore interventions that specifically target suicidal young people are required. Good evidence exists regarding the treatment of youth depression [15], but there is limited knowledge regarding effective interventions for suicide-related behaviour [7,8]. Of the psychological approaches that have been tested Cognitive Behavioural Therapy (CBT) appears to be the most promising in terms of its ability to reduce suicidal ideation among adolescents and young adults, however further research is required [8].

CBT is used extensively in the treatment of adolescent depression [16] and is recommended as a first-line treatment for depressed youth [17]. Components frequently used with depressed adolescents include: basic psycho-education; pleasant activity scheduling; cognitive restructuring; problem-solving; and relaxation training [16].

In response to the growing popularity of electronic means of communication, in particular among youth, CBT interventions are now routinely delivered via the Internet. Internet-based CBT has been shown to be an effective and cost-effective form of treatment for depression and anxiety among adults [18-24], and has the potential to be more accessible and less stigmatising than traditional, face-to-face models of therapy [25,26]. It has also been shown to have the potential both to prevent and reduce symptoms of depression and anxiety in adolescents [27,28].

Adherence has been highlighted as a particular issue with online interventions [29]. There is evidence to suggest that programs that are password protected, practitioner prescribed and supported, tend to have higher rates of adherence, lower rates of attrition and better treatment outcomes than open access sites [23,30].

Given that practitioner involvement appears to improve outcomes, and that school wellbeing staff are considered helpful by students when it comes to mental health-related difficulties [31], the development of an Internet-based CBT program that can be delivered by school wellbeing staff is a logical next step. Indeed schools are an obvious and accepted environment for implementing suicide prevention initiatives [11,32-34].

Yet, despite the potential benefits of Internet-based CBT, there is virtually no research into the impact of Internet-based CBT on SRB. To date only one study specifically set out to test the effects of an Internet-based program among suicidal adults, and reported a reduction in SI [35], and two studies testing online interventions for depression also demonstrated a reduction in suicide-related outcomes [36,37]. No studies have targeted suicidal youth.

In response to this, we have developed and piloted an Internet-based program for school students at risk of suicide called Reframe-IT. Reframe-IT has been specifically designed for young people, and unlike other Internet-based programs, is designed to be delivered and supported, by school wellbeing staff.

The program has been piloted with 21 young people from nine schools. Findings show a reduction in suicidal ideation, depressive symptoms and hopelessness [38], and an increase in problem solving and coping skills (Hetrick et al, forthcoming) over the course of the program. The data also show that the modules do not induce either distress or suicidal ideation, and overall participants report finding the program enjoyable and say that they would recommend it to a friend [39]. The pilot study was small and uncontrolled, therefore the program requires testing in a randomised controlled trial to confirm its effectiveness.

## Methods

### Aims

The primary aim of this study is to examine whether or not participation in the Reframe-IT program leads to reduced: 1) suicidal ideation. Additional aims are to examine its impact on: 2) symptoms of depression, and 3) levels of hopelessness, among participating students, and to determine if it leads to: 4) increased confidence 5) increases in perceived skill, and 6) changes in practice among school wellbeing staff (in particular with regard to their use of Internet-based programs and resources with at-risk students).

### Study design

The student-related aims listed above will be addressed via a randomised-controlled trial. The study has a staggered two-year recruitment phase and involves the delivery of eight modules of CBT delivered over a 10-week intervention period. Students are followed up post intervention and again 12 weeks later. The study has been designed in order that the CONSORT guidelines [40] can be met when reporting the trial.

The aims related to school staff will be assessed using a pre-test/post-test design.

The study team comprises a project coordinator (JR), a research therapist (SH); two research assistants; a clinical psychologist (SB), and a statistician ([name]).

### Recruitment

All secondary schools in the study catchment area (north west metropolitan Melbourne) will be invited to participate. Up to 28 of the responding schools will be selected on a first-come first-served basis. Schools will be recruited in a staggered manner. Participants (n = 170) will also be recruited in a staggered manner, over a two-year period. In order to meet the inclusion criteria students must be aged 14 to 18 and report any level of SI in the past month. They must also provide written consent from themselves and their parents/guardians. Exclusion criteria are an intellectual disability, psychotic symptoms and/or inability to speak English. Participants will be recruited by members of the student wellbeing team at each school. All students who present to the school wellbeing staff member and meet the inclusion criteria will be asked if they are interested in hearing more about the study by that staff member. They will also be given a brief information sheet explaining the study, which they can read and share with their parents/guardian. If the student indicates that they would like to take part they are given a detailed information and consent form to take home to be signed.

Withdrawal from the study will occur if participation in the study interferes with clinical management of risk, or if the participant develops psychotic symptoms.The participant flow chart is shown in Figure 1.

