### Intervention

The Reframe-IT intervention comprises eight modules to be delivered during the 10-week intervention period. Each participant will have access to his or her own personalised webpage accessed via secure login. For safety reasons, the program will be administered in the young person’s school by the student wellbeing staff member. Once each individual module has been completed in the presence of the school staff member, participants will be able to access it from home, 24 hours a day. The program has no social networking function.

The program takes the form of an adult ‘host’ character that delivers the therapy verbally, and a series of video diaries made by young people. There are two activities per week plus homework. The site has a message board through which the participant can communicate with the research-therapist; a series of factsheets covering a range of related topics, including managing suicidal thoughts; plus downloadable relaxation MP3s. As the weeks progress additional items are added to the site, (e.g. an activity diary). Finally there is a ‘Getting help’ tab, which lists a range of local and national helplines and services that the participant can access if in crisis.

The eight modules incorporate standard CBT approaches commonly used with young people but have a specific focus on suicidal thinking and behaviours [16]: engagement and agenda setting; emotional recognition and distress tolerance; identification of negative automatic thinking; behavioural activation - help-seeking and activity scheduling (including relaxation techniques); problem solving; detecting and challenging problematic thinking, and cognitive restructuring.

Practitioner involvement will be two-fold. First, the SWC will facilitate delivery of the program (i.e. setting up appointments; managing Internet issues; and remaining in the vicinity while the participant views the program). They will also check responses to a weekly suicide screen and respond accordingly. Second, there will be involvement from the research therapist (SH) who will remain un-blinded. She will check completed activities and respond with personalised but standardised messages. She will also check the message board daily and respond accordingly.

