### Control intervention

The control group will receive Treatment As Usual only. This will be monitored via questionnaire, and a weekly client contact sheet completed with each school.

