### Blinding and treatment fidelity

Because of the nature of the intervention (i.e. it is to be delivered by school staff) it is not possible for school staff to be blind to intervention. In addition, the study coordinator (JR) and the two study psychologists (SH and SB) will remain unblinded in order that randomisation can be conducted and to enable the website to be moderated. However the research assistants conducting outcome assessments and the statistician conducting the analysis will remain blinded to treatment allocation until study completion.

With regard to treatment fidelity, a study manual has been developed to facilitate this across sites. However it is acknowledged that the same school staff will be administering both the treatment and control interventions to students. Therefore there is the possibility of some contamination, in terms of school wellbeing staff incorporating some of the techniques from the CBT program into their work with students allocated to the control condition. However we consider this to be unlikely. Although school staff will be responsible for administering the program, they will not be required to supervise the student closely whilst they watch the program. Rather their role will be to set up appointments with the students, to remain in the vicinity whilst each module is completed, and to check the suicidal ideation screen at the end of each module. However in order to assess this we will ask all school wellbeing staff to complete a short checklist at the end of each session with a Reframe-IT student that will record the length and content of each session.

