#### Protocols and supervision

Clear and detailed safety protocols have been developed for this study detailing how undue risk will be determined and how the research team will respond. The research assistants will receive training in the administration of the measures and in the assessment of suicide risk. The research assistant will make contact with the school wellbeing staff member once each assessment is completed. If the research assistant and the school are concerned about the participant the project coordinator will be informed and, where necessary, an immediate referral will be made to an appropriate service. Fortnightly supervision meetings with the research therapist and the clinical psychologist will be held, during which all cases will be presented and any diagnostic and/or risk issues discussed.

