#### Weekly screening

In addition, participants will complete a weekly suicidal ideation screen, which will be checked by the school wellbeing staff member at the end of each session. If a participant indicates current suicidal ideation, a risk assessment will be conducted. If they are determined to be at elevated risk then the staff member will be required to follow the school’s safety protocols. They will also receive an automated email prompting them to follow these procedures.

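### Students who meet the withdrawal criteria leave the whole study, and nothing says their outcomes are still collected; if this happens more often in one arm, the primary comparison could be biased

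*Protocol article*

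**What the plan says.** The rule stands in the Recruitment section of the protocol article: "Withdrawal from the study will occur if participation in the study interferes with clinical management of risk, or if the participant develops psychotic symptoms". It is mandatory and names the study. Students are assessed at baseline, at 10 weeks and 12 weeks after that. The sample size section describes efforts to keep students in follow-up, but does not say that these cover students withdrawn under the rule.

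On how risk is detected:

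- The Intervention section lists a suicide screen among the school staff member's delivery tasks: "They will also check responses to a weekly suicide screen and respond accordingly". Blinding and treatment fidelity places it with the modules: "to check the suicidal ideation screen at the end of each module".
- Weekly screening names no arm, but ties the screen to sessions: "participants will complete a weekly suicidal ideation screen, which will be checked by the school wellbeing staff member at the end of each session". The stated consequence of elevated risk is: "If they are determined to be at elevated risk then the staff member will be required to follow the school’s safety protocols".
- For controls: "The control group will receive Treatment As Usual only". The monitoring described is: "This will be monitored via questionnaire, and a weekly client contact sheet completed with each school". No suicide screen is named there.
- One route is common to both arms (Protocols and supervision): "The research assistant will make contact with the school wellbeing staff member once each assessment is completed".

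The Statistical analysis section compares arms at each time point with a general linear model adjusted for the baseline score. It names last observation carried forward and multiple imputation as options should many values be missing.

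**The concern.** The primary outcome is suicidal ideation. One trigger for leaving the study is a conflict with the management of suicide risk; the other is emerging psychosis. Rising risk is a likely route to the first. The students who leave may therefore be those whose later SIQ would have been high and in whom suicidal acts are most likely, and as written their 10- and 22-week data are not sought.

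The direction of any bias depends on whether withdrawal differs by arm. There are reasons to think it might. The screen is described with the modules, school staff are not blinded, and a control student's study participation beyond usual care amounts to little more than the assessments and questionnaires, so there is less that could interfere with care. If more high-risk students leave the intervention arm, the observed SIQ difference moves in its favour.

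Whatever the balance between arms, the trial would lack follow-up data on students who are informative about harm. Outcomes that were never collected cannot be recovered at analysis.

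**Working it through.** **1. The plan's own figures.** With alpha 0.05 (two-sided assumed), power 0.80, a medium effect taken as 0.5 SD (the article gives no number) and a covariate explaining 10% of variance, the normal approximation gives 57 per group. The exact t calculation gives power 0.797 at 57 and 0.803 at 58, so the stated 58 reproduces. Then 2 × 58 = 116; 116 × 1.1 = 127.6, rounded up to 128; 128/0.76 = 168.4, rounded up to 169. No stated number is wrong. The 24% dropout allowance covers lost numbers. It is not split by arm or reason, and it does not address bias.

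**2. Simple bias formula.** If a share w of an arm is removed and those students lie k SD above the full arm mean, the mean of those remaining shifts by −wk/(1−w). The bias in the difference is the intervention shift minus the control shift. The article gives no withdrawal rates or offsets, so these are assumptions: 5–10% intervention, 0–5% control, k = 1 to 1.5. With 170/2 = 85 per arm, 5% is about 4 students and 10% about 8 or 9.

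| Withdrawn, intervention / control | k = 1 | k = 1.5 |
|---|---|---|
| 5% / 5% | 0 | 0 |
| 5% / 0% | −0.053 | −0.079 |
| 10% / 5% | −0.111 + 0.053 = −0.058 | −0.167 + 0.079 = −0.088 |
| 10% / 0% | −0.111 | −0.167 |

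Negative values favour the intervention. The range is 0 to about 0.17 SD; at the upper end 0.167/0.5 = 33% of the assumed effect.

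**3. Check with baseline adjustment.** A simulation of 2 million students with no true effect, analysed with baseline as covariate (R² = 0.10), removed students by worsening from baseline, by worsening plus noise, or by the follow-up score itself.

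| Withdrawn, intervention / control | Complete-case bias (SD) |
|---|---|
| 2% / 0% | −0.03 to −0.04 |
| 5% / 2% | −0.03 to −0.05 |
| 5% / 0% | −0.06 to −0.10 |
| 10% / 5% | −0.05 to −0.08 |
| 10% / 2% | −0.08 to −0.13 |
| 5% / 5% | 0.00 |

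The baseline covariate does not remove the bias. Last observation carried forward gives −0.02 to −0.15 over the same unequal scenarios, because it puts an earlier score in place of a worsened one. Multiple imputation was not simulated separately. If it uses baseline and arm and assumes data are missing at random, it should behave about like the complete-case analysis. With R² = 0.36 every unequal scenario keeps its sign.

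**4. Effect on false positives.** With 58 per group and R² = 0.10, treating students as independent, a bias of 0.10 SD raises the two-sided rejection rate under no effect from 5% to about 8.7%; 0.15 SD raises it to about 13.5%.

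**The case against.** A reader might infer that students are withdrawn because they worsen, that this happens more in the intervention arm, and that the result is therefore biased. The article does not support that chain as fact.

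- The risk trigger is a conflict between participation and clinical care, not a worse score. Where the article says what follows raised risk, it names the school's safety protocols or a referral, not withdrawal.
- More frequent screening does not establish more withdrawal. The safety section names no arm for the screen, and risk is discussed with the school after assessments in both arms. The weekly screen concerns suicidal ideation, so it gives no reason for unequal withdrawal for psychosis.
- With equal withdrawal, the between-arm bias under no effect is about zero. The rates and offsets used above are assumed.
- The article condenses a fuller protocol and refers to safety protocols that are not shown. It aims at CONSORT reporting, which would largely cover withdrawals by arm and reason. An independent committee oversees safety and can suspend the trial.

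All of this stands, and it makes the direction and size conditional. It does not remove the core point. The rule is stated, not left open; it ends study participation; its triggers are plausibly related to the outcome; and nothing shown keeps outcome collection going. Safety oversight and interim analyses would also lack the follow-up data of these students.

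**Conclusion.** The point holds in conditional form. The withdrawal rule as written can make outcomes missing because of the student's condition, and the named analyses would not repair that. Bias towards the intervention arises if withdrawal is more frequent in that arm. The descriptions of screening make this plausible, but it remains an inference.

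Under the assumptions in the working, the bias lies between 0 and about 0.17 SD, against an assumed target of 0.5 SD. It is probably small unless the arms differ by several percentage points. It would be wrong to say that the trial is biased, or to quote a range that leaves out zero. Equal withdrawal removes the between-arm bias under no effect, but not the loss of SIQ and suicidal-acts data on these students.

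**What to change.** Leave the clinical criteria as they are. Add wording that separates stopping study treatment from leaving follow-up, and apply it to both arms. Controls have no program to stop, so for them meeting a criterion would simply not end outcome collection.

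- Seek the 10- and 22-week SIQ and the suicidal-acts questions from students who meet the criteria, unless consent is withdrawn or the treating team objects to the assessment.
- Analyse these students in their randomised arm.
- Record and report such withdrawals by arm and reason.

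If some outcomes are still missing for these reasons, a sensitivity analysis that does not assume missing at random would show how far the result depends on them.

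The cost is a wording change and a few additional follow-up contacts, some with students under acute care, through the school, phone, email and parent channels already planned. The sample size does not change.

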**Figure 1 F1:**
[figure not shown]
Study flow-chart.

### Intervention

The Reframe-IT intervention comprises eight modules to be delivered during the 10-week intervention period. Each participant will have access to his or her own personalised webpage accessed via secure login. For safety reasons, the program will be administered in the young person’s school by the student wellbeing staff member. Once each individual module has been completed in the presence of the school staff member, participants will be able to access it from home, 24 hours a day. The program has no social networking function.

The program takes the form of an adult ‘host’ character that delivers the therapy verbally, and a series of video diaries made by young people. There are two activities per week plus homework. The site has a message board through which the participant can communicate with the research-therapist; a series of factsheets covering a range of related topics, including managing suicidal thoughts; plus downloadable relaxation MP3s. As the weeks progress additional items are added to the site, (e.g. an activity diary). Finally there is a ‘Getting help’ tab, which lists a range of local and national helplines and services that the participant can access if in crisis.

The eight modules incorporate standard CBT approaches commonly used with young people but have a specific focus on suicidal thinking and behaviours [16]: engagement and agenda setting; emotional recognition and distress tolerance; identification of negative automatic thinking; behavioural activation - help-seeking and activity scheduling (including relaxation techniques); problem solving; detecting and challenging problematic thinking, and cognitive restructuring.

Practitioner involvement will be two-fold. First, the SWC will facilitate delivery of the program (i.e. setting up appointments; managing Internet issues; and remaining in the vicinity while the participant views the program). They will also check responses to a weekly suicide screen and respond accordingly. Second, there will be involvement from the research therapist (SH) who will remain un-blinded. She will check completed activities and respond with personalised but standardised messages. She will also check the message board daily and respond accordingly.

